#### Secondary endpoints

Secondary endpoints are parasitic clearance at weeks 1, 2, 4, and 8 during the treatment period and at 4, 6, and 8 months during the follow-up period, measured by qualitative PCR. Serological response will be assessed by conventional serology at 12-month follow-up. The proportion of HLA-B*3505 carriers among the patients who experience SAEs will be recorded, as will blood concentrations of BNZ at 15 d and by the end of treatment.

### Patient eligibility

Patients aged ≥ 18 years having any combination of at least two positive serologic test results against *T. cruzi* (indirect immunofluorescence, indirect hemagglutination, or ELISA) and not having previously received treatment with BNZ or nifurtimox (either completely or partially) will be eligible. Inclusion and exclusion criteria are summarized in Tables 1 and 2, respectively.

**Table 1 Tab1:** Inclusion criteria

Inclusion criteria (patients should meet all criteria)	
• Adults ≥ 18 years old	
• Have been diagnosed with Chagas disease by two positive serological tests using different antigens	
• Have detectable *Trypanosoma cruzi* DNA in peripheral blood through a qualitative interpretation of the polymerase chain reaction technique	
• Written informed consent provided	
• Weight ≥ 50 kg and ≤ 80 kg	
• Ability to comply with all tests and specified protocol visits and have a permanent address	
• Patients must be residents of areas free of vector transmission (*Triatoma infestans*), defined by local health programs or by the Pan American Health Organization/World Health Organization definition.	
• Women of childbearing age should have a urine or serum negative pregnancy test at the moment of the baseline visit. Breastfeeding should not be allowed, and a barrier method of contraception should be used during the treatment phase.

**Table 2 Tab2:** Exclusion criteria

Exclusion criteria	
• Having previously received treatment with benznidazole or nifurtimox (either completely or incompletely)	
• Signs and/or symptoms of severe cardiac form of Chagas disease (as confirmed by local national guidelines)	
• Impossibility to complete the specified protocol follow-up visits	
• Acute or chronic health problems that, in the opinion of the principal investigator, may interfere with the evaluation of the efficacy and/or safety related to the drug (for example, acute infections, human immunodeficiency virus infection, liver or kidney disease)	
• History of alcohol abuse	
• Known hypersensitivity to metronidazole drugs	
• Concomitant use or history of use of allopurinol, antimicrobial, antiparasitic, or antifungal agents	
• Having laboratory parameters outside the range of normal or that are considered clinically relevant by the responsible physician: ◦ Total leukocyte count must be within the normal range, with an acceptable range of ± 5%. ◦ Total platelet count must be within the normal range up to 550,000/mm^3^ or 550 × 10^9^/L. ◦ Total bilirubin must be within the normal range. ◦ Transaminase levels must be within the normal range, with an acceptable range of 25% above the upper limit of normal (ULN). ◦ Total creatinine level must be within the normal range, with an acceptable variation of 10% above the ULN. ◦ Alkaline phosphatase level must be within the normal range up to < 2.5× ULN. ◦ Gamma glutamyl transferase level must be within the normal range up to 2× ULN. ◦ Fasting glucose must be within the normal range.	

### Randomization and follow-up

Patients are randomly assigned to receive BNZ 150 mg/day for 60 days, 400 mg/day for 15 days, or the standard scheme of 300 mg/day for 60 days. Because this is a double-blind trial, investigators and all sponsor staff will not be aware of the treatment allocation and randomization list until the end of the trial. Double-blinding will be adopted for all trial arms. Patients will be randomized 1:1:1, and randomization will be done via a remote and interactive response system, according to a predefined list. To avoid bias, randomization will be centralized and concealed. The treatment groups will be allocated on day 1 on the basis of a balanced block randomization, taking into account the country. Each patient will be assigned an identification code that will correspond to the trial kit number allocated to the patient. The label will indicate the trial number and the number of the kit, but it will not indicate the treatment designation.

Scheduled follow-up visits will occur at 7, 15, 28, and 60 days and up to 4, 6, 8, and 12 months after initiation of treatment. More information is provided in Fig. 1.

**Fig. 1 Fig1:**
[figure not shown]
Clinical trial design. *BNZ* Benznidazole, *BV* Baseline visit, *EoF* End of follow-up, *FV* Follow-up visit, *SV* Screening visit, *TV* Treatment visit

### Sample size and data analysis

For the sample size calculation, we considered a superiority design for two-sample comparison of proportions. We hypothesize a reduction of 50% of the total number of patients who either have a positive PCR result during follow-up or have to discontinue the treatment due to AEs, has been taken into account as a hypothesis. It is estimated that in the standard arm of treatment, 40% of patients will be evaluated as treatment failures according to the intention-to-treat principle.

Given the expected proportions in every group and given that we plan two pairwise comparisons for a power of 80% and a type I error of 0.05, the total number of patients that should be included in the study is 240, which will comprise 60 participants per country.

The categorical data will be presented as absolute numbers and proportions, and the continuous variables will be expressed as means and standard deviations when normal distribution is demonstrated (using the Kolmogorov-Smirnov test) or as medians and interquartile ranges when it is not.

For comparison of the distribution of categorical variables, the χ^2^ test or Fisher’s exact test will be used, and the Mann-Whitney *U* test or Student’s *t* test will be used for continuous variables, respectively, depending on the presence or not of normal distribution.

A comparative analysis of the main clinicoepidemiological variable among the three groups will be carried out. The primary efficacy analysis will be the comparison of the proportion of patients with sustained parasitologic clearance of each treatment arm compared with the standard arm of treatment. The time until the first positive PCR result for *T. cruzi* will be evaluated by Kaplan-Meier survival analysis with the log-rank test for significance.

The proportion of patients with SAEs and/or AEs leading to treatment discontinuation will be described per trial arm and by System Organ Class (using preferred terms defined by MedDRA 13.1), according to the National Cancer Institute’s Common Terminology Criteria for Adverse Events (version 4.03). Incidence rate and 95% confidence interval will be presented per trial arm for SAEs and AEs per category, along with the most frequent AEs.

Safety laboratory parameters (hematology and biochemistry) will also be described individually per trial arm, showing the proportion of patients by degree of elevation relative to upper limit of normal and baseline values, as well as blood level changes over time.

Safety data will be correlated to efficacy and treatment compliance data and to PK parameters. Differences in the rate of absorption in serology will be estimated with *t* test pairs or the Wilcoxon test, depending on their distribution. All safety analyses will be carried out on all patients treated, understood as all patients who receive at least one dose of treatment. Finally, the sensitivity, specificity, and positive and negative predictive values of the presence of HLA-B*3505 and their relationship with the occurrence of SAEs will be calculated.

The efficacy analysis will be carried out according to the intention-to-treat principle. The group of patients analyzed will be all randomized patients in each of the treatment branches. Cases lost during follow-up and dropouts will be considered treatment failures.In addition, a per-protocol analysis will be defined as all patients receiving randomized treatment who meet the main criteria, have not permanently left the administration of the treatment, and have no other protocol deviation. Patients lost to follow-up will be excluded unless they present a positive PCR result, in which case, they will be included in the analysis. The results will be analyzed using IBM SPSS Statistics version 19.0 software (IBM Corp., Armonk, NY, USA).

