Currently, there are only two available drugs to treat CD: nifurtimox and benznidazole (BNZ). Of these two, BNZ is the one most studied and most often used as a treatment. However, current schemes of this treatment have some limitations. On the one hand, it has a limited efficacy based on seroconversion (around 50–80% in the acute phase of the disease and 8–20% in the chronic phase) [7]. Another important limitation is the high rate of adverse events (AEs) when using these drugs. The incidence of AEs related to BNZ varies from 40–50% up to 98%, and around 15% of these patients have to definitively stop the treatment for this reason, with the rate even higher in patients treated with nifurtimox [8–10]. The most commonly observed AEs are hypersensitivity (rash, fever, generalized edema, lymphadenopathy, myalgia, and arthralgia), gastrointestinal disorders, bone marrow toxicity (neutropenia and thrombocytopenic purpura), and peripheral polyneuropathy [9]. Current knowledge about the BNZ toxicity mechanisms is scarce because the main studies have focused on the clinical aspects of these AEs [10]. Our group recently carried out an analysis of the cytokine profile and human leukocyte antigen (HLA) classes I and II of patients who were treated with BNZ, and we found a higher treatment discontinuation rate due to skin hypersensitivity AEs in patients who had the HLA-B*3505 allele [11].

Moreover, another drawback of the studies assessing the efficacy of BNZ in chronic CD is the lack of a biomarker to define the cure of disease. Currently, the cure criteria are negative seroconversion of two serologic assays against different antigens, but it usually takes several years after an effective treatment, precluding its use in clinical trials. In addition, detection of *T. cruzi* DNA in peripheral blood cannot be used to define cure, because a negative result does not mean absence of the infection; however, in recent years, it has become an important tool used to identify therapeutic failure when the result remains positive after completed treatment [8].

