#### Primary endpoints

The primary endpoint is parasitologic response, defined as maintained negative qualitative PCR results during the 12-month follow-up period. For efficacy assessments, the end of treatment of each treatment arm will be defined in accordance with the duration of the treatment regimen. Incidence and severity of AEs and those leading to treatment discontinuation will also be recorded.

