### SAEs and unblinding: care of patients with AEs

All AEs and other study outcomes in the randomization, treatment, and follow-up periods will have to be reported. In case of mild or moderate AEs, the administration of BNZ will be suspended temporarily according to the clinical researcher’s decision. Symptomatic treatment will be provided to the patient according to the treating physician.

It will be considered that a patient has finished the study when he or she has completed the treatment and follow-up phase (per-protocol principle). The study may be interrupted in case of voluntary decision of the patient at any time if an AE forces interruption of the treatment, if significant protocol violations occur, or if the treating physician deems it would benefit the patient (intention-to-treat principle).

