In addition, the mechanisms underlying BNZ toxicity are still not well understood. The production of several metabolites in the enzymatic reduction of the drug, their accumulation, and their interactions with cellular constituents could be the main reasons for producing these AEs [32, 33]. Some AEs of the drug have a certain temporal pattern. For example, dermatological and digestive manifestations usually tend to occur around day 10 of treatment, while neurological events and arthritis appear after day 40 of treatment, probably because they are related to the cumulative total dose and not to the serum concentration [9]. Age and female sex have also been considered as classic risk factor for AEs. However, there remains an important lack of knowledge about the mechanisms of toxicity [9, 10].

According to the duration of the treatment, two approaches were considered. Taking into account the cure rates of patients with CD treated with shorter courses of BNZ (those who had to interrupt the treatment because of AEs), a shortened regimen has been incorporated. Finally, researchers explored the possibility of including a new arm with prolonged exposure. Unfortunately, due to the lack of clinical published experience and the potential risk of gonadal toxicity and its effect over the pituitary–testicular axis, that treatment arm was discarded [34, 35].

Another aspect that will be assessed is the genetic variability of the parasite over the treatment response. The great majority of randomized clinical trials have been conducted in Argentinean or Bolivian patients, and scarce information is available in other geographical regions. In any case, the few existing data suggest an important effect of parasitic diversity in the treatment efficacy and response [17, 36].

Therefore, this clinical trial will evaluate the efficacy and safety of different dosing regimens of BNZ compared with the standard treatment scheme. Experimental dosing regimens have been chosen on the basis of evidence derived from previous studies, in which it has been found that shorter-duration schemes and/or lower dose with the same duration could achieve the same cure rate. Moreover, higher doses could be used without entailing a higher rate of AEs. The results of this clinical trial will help to better identify the most adequate BNZ regimen in terms of efficacy and safety for the treatment of CD in the chronic phase.

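### The 80% power is calculated for a composite failure (positive PCR or stopping for an adverse event), but the primary endpoint is written as PCR alone, so that power is not established for it

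*Protocol article*

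**What the plan says.** All references are to the protocol article.

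- **Sizing** (Sample size and data analysis). The text states that "we considered a superiority design for two-sample comparison of proportions". The event is "patients who either have a positive PCR result during follow-up or have to discontinue the treatment due to AEs". It is put at 40% in the standard arm, described as treatment failure under intention to treat, and is assumed to fall by half. With 80% power, type I error 0.05 and two pairwise comparisons, the total is 240.
- **Endpoint** (Primary endpoints). "The primary endpoint is parasitologic response, defined as maintained negative qualitative PCR results during the 12-month follow-up period". The primary outcome under Outcomes and endpoints is also defined by PCR, and tolerability is listed there as a secondary objective.
- **Primary analysis** (Sample size and data analysis). "The primary efficacy analysis will be the comparison of the proportion of patients with sustained parasitologic clearance", each arm against standard. AEs leading to discontinuation are described separately by arm.
- **Intention-to-treat rule** (same section). "Cases lost during follow-up and dropouts will be considered treatment failures". The article does not define a dropout.
- **After an AE stop.** Under Study organization, the follow-up phase begins at the last dose, including when a severe AE ends treatment, and runs to 12 months after randomization with PCR visits. Under SAEs and unblinding, participation may be interrupted "if an AE forces interruption of the treatment", and that sentence is labelled with the intention-to-treat principle.

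**The concern.** Take a patient who stops treatment for an AE and stays PCR-negative to month 12. The sizing counts this patient as a failure. The endpoint definition, read literally, counts the same patient as a responder. No section says which classification the primary analysis will use.

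Two things are at stake. First, the 80% is a property claimed for the primary comparison but calculated for a different event. Second, AE stops are not rare: the Introduction says of benznidazole-related AEs that "around 15% of these patients have to definitively stop the treatment for this reason". If the classification of these patients stays open, it could be settled after results are known, and it could affect the primary result.

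**Working it through.** **Inputs from the article.** 240 patients randomized 1:1:1, so 240/3 = 80 per arm; composite failure 40% against 40% × 0.5 = 20%; type I error 0.05. Sidedness is not stated; two-sided is assumed.

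**Inputs assumed.** The article does not split the 40% into PCR and AE parts. The 15% in the Introduction is background and not a sizing input. It is used here only to centre an illustration with a range of 10 to 20 points.

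**Formulas** (two proportions, pooled variance under the null, no continuity correction; p̄ is the mean of p1 and p2, d = p1 − p2):

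- n per arm = [1.96·√(2p̄(1−p̄)) + 0.8416·√(p1(1−p1)+p2(1−p2))]² / d²
- power = Φ{[d·√n − 1.96·√(2p̄(1−p̄))] / √(p1(1−p1)+p2(1−p2))}

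**Step 1: the plan's own figure.** For 0.40 v 0.20:

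- n = [1.96·√0.42 + 0.8416·√0.40]² / 0.04 = (1.270 + 0.532)² / 0.04, about 81.2, so 82 per arm and 246 in total. The arcsine formula gives 80.3 per arm, or about 240.
- Power at 80 per arm = Φ[(0.2·√80 − 1.270)/0.632] = Φ(0.820) = 0.794.

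The 240 and the 80% therefore reproduce for the composite at an unsplit two-sided 0.05.

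**Step 2: PCR alone, with PCR failure halved.** If AE-only failures (stopped for an AE, never PCR-positive) are s points of the 40, PCR failure in the standard arm is 40 − s.

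| AE-only share s | PCR failure, standard v experimental | Power at 80 per arm | Total for 80% power |
|---|---|---|---|
| 10 points | 30% v 15% | 0.62 | 363 |
| 15 points | 25% v 12.5% | 0.53 | 456 |
| 20 points | 20% v 10% | 0.42 | 597 |

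The 15-point row in full: p̄ = 0.1875; power = Φ[(0.125·√80 − 1.96·√0.3047)/√0.2969] = Φ[(1.118 − 1.082)/0.545] = Φ(0.066) = 0.53.

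**Step 3: allow overlap.** If 15% stop for AEs independently of PCR failure q, then 1 − (1 − q)(0.85) = 0.40. This gives q = 1 − 0.60/0.85 = 29.4%, halved to 14.7%. Power is 0.61, and 80% power needs 124 per arm (372 in total).

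**Step 4: hold the composite at 40% v 20% and vary the source of the benefit.** With a 15-point AE-only share in the standard arm, if the experimental regimen removes a fraction x of AE-only failures, its PCR failure is 20 − 15(1 − x) points.

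| x | PCR failure, standard v experimental | Power |
|---|---|---|
| 0 | 25% v 5% | 0.95 |
| 0.5 | 25% v 12.5% | 0.53 |
| 1 | 25% v 20% | 0.11 |

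The same composite assumption is thus compatible with PCR-only power from about 0.11 to 0.95.

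**The case against.** The strongest reply is that the primary analysis follows intention to treat and may not be purely PCR. The rule names losses and dropouts separately, so dropouts may well mean patients who abandon treatment. The 40% is itself described in intention-to-treat terms, and the section on SAEs ties an AE-forced interruption to the same principle. On that reading the analysed failure is close to the sized composite, and the 80% applies.

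This part stands: the text does not prove that such a patient would be analysed as a success. It does not remove the problem. The Study organization section keeps patients in PCR follow-up after an AE stop. The per-protocol definition uses different words for leaving treatment and does not call it dropping out. The endpoint definition has no AE component. A separate analysis plan might define dropouts, but the article's endpoint and its sizing event would still differ.

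A reader might also infer that the trial is under-powered, at about 53%. The article does not support that as a fact. The 15% is background, subtracting it from 40% assumes no overlap with PCR failure, and Step 4 shows that even the direction of the change is not fixed.

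Nor does it follow that failures could be halved only through fewer AE stops. The Discussion does say that "shorter-duration schemes and/or lower dose with the same duration could achieve the same cure rate". It also says efficacy seems to depend on concentration, and the Higher dose section gives a dose-dependence argument, so a parasitological benefit is part of the rationale for the 400 mg arm.

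**Conclusion.** The sizing event and the written primary endpoint differ, and no section reconciles them. The stated 80% is right for the composite (0.794 at 80 per arm, two-sided 0.05) and not established for the PCR endpoint.

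If AE-only failures are 10 to 20 of the 40 points and PCR failure is halved, power is about 0.62 to 0.42 (0.53 at 15 points; 0.61 if 15% stop for AEs independently of PCR failure). These figures rest on assumptions that the article neither makes nor excludes. They show how much depends on the classification; they do not estimate the trial's actual power.

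**What to change.** Before unblinding, choose one of the following.

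**(a)** Write the sized event into the Primary endpoints section, so that a permanent stop of the assigned treatment for an AE counts as failure alongside a positive PCR. Make PCR alone a secondary endpoint. The 80% then refers to the event that was sized. The cost is a primary endpoint that mixes efficacy and tolerability. The definition must also say over which days a stop counts, because the assigned regimens last 15 or 60 days.

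**(b)** Keep PCR alone as primary. State that patients who stop for an AE remain in follow-up for the endpoint and are classified by PCR. Give the assumed PCR-only failure rates, and replace the 80% with the power that 80 per arm gives for those rates. The cost is a stated power that may be less favourable, and a need to obtain PCR results from patients who stopped.

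Under either choice, define dropouts and bring the endpoint definition, the sample-size paragraph, the intention-to-treat rule, the follow-up phase text and the section on SAEs and unblinding into agreement. This is mainly a change of wording: PCR results and AE discontinuations are already to be recorded. The exception is any patient whose participation ended at an AE stop, for whom later PCR results may be missing.

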#### PCR

Laboratories included in the project will carry out the same reverse transcriptase (RT)-PCR protocol following the instructions included in the laboratory manual agreed among all of them. To carry out this technique, 5 ml of whole blood will be collected and mixed with 5 ml of guanidine hydrochloride 6 M–ethylenediaminetetraacetic acid 0.2 M for a minimum of 72 h at room temperature. Three DNA extractions will be performed using the manual column method (High Pure PCR Template Preparation Kit; Roche Diagnostics, Mannheim, Germany), except in Spanish centers (Vall d´Hebron University Hospital and Ramón y Cajal University Hospital) where DNA extraction will also be done in triplicate using an automated extraction method (NucliSens easyMAG, bioMèrieux, Marcy l’Etoile, France).The consensual PCR protocol consists of a real-time multiple PCR (Duffy et al. 2013) [30] that allows the amplification of a *T. cruzi* satellite DNA region and a linearized recombinant plasmid used as an internal amplification control. The RT-PCR will be carried out in duplicate from each of the extractions. At least one amplification of the six performed with an amplification cycle (cycle threshold) of *T. cruzi* below 40 and a correct value of Internal Amplification Control (IAC) will be interpreted as positive. To be correct, the values of the IAC must meet Tukey’s criteria.

To assess the homogeneity of the results obtained by the different laboratories, a harmonization panel consisting of ten tubes containing blood with uninfected guanidine and infected with 1, 10, and 100 parasitic equivalents per milliliter of *T. cruzi* strains TcV and TcVI was processed. The samples were processed blindly by the different laboratories, and the results were evaluated by an external center in charge of providing the panel and analyzing the results (Instituto de Investigaciones en Ingeniería Genética y Biología Molecular, Buenos Aires, Argentina). On the other hand, and following the same work scheme, four external quality control panels will be analyzed during the study period.

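### Allocation is blocked by country, but the tests named for the primary comparison and the log-rank analysis do not use country, so efficiency is forgone if country is prognostic

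*Protocol article*

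**What the plan says.** **Allocation.** The Randomization and follow-up section assigns patients 1:1:1 "on the basis of a balanced block randomization, taking into account the country". The Sample size and data analysis section sets 240 patients in total, 60 per country, which is about 20 per arm per country and 80 per arm.

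**Primary comparison.** The same section states: "The primary efficacy analysis will be the comparison of the proportion of patients with sustained parasitologic clearance of each treatment arm", each set against the standard arm. That sentence names no test. A general clause just before it gives chi-square or Fisher's exact for categorical variables. Time to first positive PCR is to be analysed by Kaplan-Meier with a log-rank test. Country appears in none of these statements.

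**Reasons country might matter.** The Discussion says that "the few existing data suggest an important effect of parasitic diversity in the treatment efficacy and response". The PCR section has the Spanish centres depart from the manual column method used elsewhere: there, "DNA extraction will also be done in triplicate using an automated extraction method". PCR defines the primary endpoint.

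**Serology.** "Differences in the rate of absorption in serology will be estimated with" what reads as a paired t test, or the Wilcoxon test, depending on distribution. Table 3 schedules serology at selection and at month 12.

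**The concern.** When allocation is balanced within a factor that predicts outcome, the arms are closer to balanced on that factor than simple randomization would make them. A test that ignores the factor still counts the between-country spread as noise. Its variance is then too large for the design, its true type I error falls below the nominal level, and it has less power than a test that uses the factor. At stake is precision in a trial sized with no slack, where losses and dropouts also count as failures.

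The serology issue is different in kind. A paired test asks whether values changed within patients. It does not ask whether a regimen differs from standard, which is the question a randomized comparison of regimens can answer.

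**Working it through.** **Inputs from the article.** Control failure: "It is estimated that in the standard arm of treatment, 40% of patients will be evaluated as treatment failures". Effect: "We hypothesize a reduction of 50% of the total number of patients who either have a positive PCR result during follow-up" or stop treatment because of adverse events, so 20% failure in an experimental arm. Error rates: "given that we plan two pairwise comparisons for a power of 80% and a type I error of 0.05". Sidedness is not stated; two-sided 0.05 per comparison is assumed here.

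**Step 1: reproduce the sample size.**
- Pooled variance: n = [1.96·√(2·0.30·0.70) + 0.8416·√(0.40·0.60 + 0.20·0.80)]² / 0.20² = (1.270 + 0.532)² / 0.04 ≈ 81.2, so 82 per arm and 246 in total.
- Unpooled variance: n = (0.24 + 0.16)·(1.96 + 0.8416)² / 0.04 = 78.5, so 79 per arm and 237 in total.

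The stated 240 lies between these. With 80 per arm the formula gives 79.4% power for one comparison.

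**Step 2: size of the plain test, by hand.** Under the null with equal country sizes, the plain test uses variance p̄(1−p̄), while the design produces the mean of p(1−p) over countries. With ratio r of the second to the first, true size is about 2·[1 − Φ(1.96/√r)]. The article gives no failure rates by country, so the rates below are assumptions, all averaging 40% (p̄(1−p̄) = 0.24).
- 25/34/45/56%: mean p(1−p) = 0.2265, r = 0.944, size about 4.4%.
- 20/30/50/60%: mean = 0.215, r = 0.896, size about 3.8%.
- 10/30/50/70%: mean = 0.190, r = 0.792, size about 2.8%.

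**Step 3: simulation.** 200,000 trials per scenario of one pairwise comparison, 20 patients per arm in each of four countries, a common odds ratio set so that mean experimental failure is 20%, and Pearson chi-square against CMH stratified by country at two-sided 0.05.

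| Control failure by country | Type I error, chi-square v CMH | Power, chi-square v CMH |
|---|---|---|
| 40% in all | 4.7% v 4.7% | 80.1% v 79.7% |
| 31/37/43/50% | 4.5% v 4.9% | 80.4% v 80.5% |
| 25/34/45/56% | 4.1% v 5.0% | 80.7% v 81.5% |
| 20/30/50/60% | 3.6% v 5.0% | 81% v 83% |
| 18/30/47/65% | 3.3% v 4.9% | 81.6% v 84.3% |
| 10/30/50/70% | 2.6% v 5.0% | 82% v 87% |
| 10/25/50/74% | 2.1% v 5.0% | 82.9% v 88.2% |

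The simulated sizes sit slightly below the hand values, in line with the 4.7% seen when there is no country effect. The plain test's power does not fall as heterogeneity grows; the stratified test's power rises away from it.

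**Step 4: serology.** With baseline to month-12 correlation ρ, and taking an unadjusted between-arm comparison of month-12 values as 1, the relative variance is 1 − ρ² for ANCOVA and 2(1 − ρ) for change scores. At an assumed ρ = 0.8 these are 0.36 and 0.40; at ρ = 0.5 they are 0.75 and 1.00. The article gives no ρ, so the size of the gain is unknown.

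**The case against.** The best case for the plan has four parts.

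- **The article is condensed.** It never says the tests are unstratified, and the link from the primary comparison to chi-square runs through a general clause. The full protocol or analysis plan may already stratify. This stands as a caution. It does not remove the mismatch between the stated allocation and the methods the article chose to name.
- **Nothing is invalid.** A reader might infer that ignoring country inflates false positives or leaves the trial underpowered against its own target. Neither holds: size only falls, and the plain test's simulated power is 80% to 83% throughout, because the planning rates are already averages over countries. This stands in full.
- **Country differences are not established.** A reader might take it as certain that failure rates will differ. The remark on parasite diversity is tentative, and no distribution of parasite types by country is given. The PCR section also describes a common protocol, triplicate extraction everywhere, a blinded harmonization panel assessed externally and four further quality control panels. A difference is plausible, no more.
- **Serology may be compared between arms.** A reader might conclude that it will be tested only within patients. The general clause giving Mann-Whitney or Student's t for continuous variables could cover an arm comparison, and it is the same clause that supplies chi-square for the primary endpoint. So the supportable statement is narrower: the only method named specifically for serology reads as paired. The 0.36 variance factor should not be quoted as the expected gain, since it rests on an assumed correlation and on a comparator the plan does not specify. Against change scores at that same correlation the gain is only 1 − 0.36/0.40 = 10%.

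**Conclusion.** The point holds as a conditional matter of efficiency. The article blocks on country and then names tests that leave country out. If country is prognostic, the power forgone against a stratified test is about 1 point for control failure of roughly 25% to 55%, 2 points for 20% to 60% and 4 to 5 points for 10% to 70%. If it is not, stratifying costs about 0.4 points.

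These figures assume equal country sizes, a common odds ratio, two-sided 0.05 per comparison and invented country rates. The direction does not depend on the exact rates. The change is worth making because the possible gain is several times the possible loss, but it is not a condition for a valid trial.

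The serology point is secondary: a baseline-adjusted comparison between regimens is not named and would be better named.

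**What to change.** Before the blind is broken, state in the analysis plan:

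1. For each experimental arm against standard, a CMH test stratified by country, reported with a country-stratified risk difference and 95% confidence interval.
2. A log-rank test stratified by country for time to first positive PCR.
3. For serology, an ANCOVA of the month-12 value (log scale if needed) on arm, baseline value and country, contrasting each regimen with standard. Keep the paired test as description of change within arms.

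If the full protocol or analysis plan already does this, a sentence confirming it is enough. The cost is a few lines of wording. Arm and country are recorded at randomization, and the ANCOVA uses the same two serology values that the paired test needs.
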